##### Safety endpoints

Report of adverse events observed throughout the studyAssessment of pain using a visual analogue scale immediately after recovery of consciousness following the postictal coma.Number of patients who have a second GTCS within 120 min after the intravenous injection

### Data monitoring

A clinical research assistant mandated by the sponsor will ensure the successful completion of the study and the collection of data generated by writing, documentation, recording, and report, in accordance with the standard operating procedures implemented at the Hospices Civils de Lyon and in accordance with good clinical practice and regulatory legislation. An independent Data and Safety Monitoring Board (DSMB) external to the trial investigators has been established specifically to monitor data throughout the study to determine if it is appropriate, from both scientific and ethical standpoints, to continue the study as planned. The DSMB will meet every year to review serious adverse events and propose continuing or stopping the study. The DSMB is made up of three experts in epilepsy ([name], Department of Clinical Neurosciences, Centre Hospitalier Universitaire Vaudois, Lausanne, Switzerland), anesthesiology ([name], Strasbourg University Hospital, Strasbourg, France), and methodology in clinical research ([name], Centre Leon Berard, Lyon, France).

### Sample size

Sample size was determined using Fisher’s exact test with a two-sided alternative hypothesis. For a significance level of 5 % (two-tailed), assuming a proportion of patients whose SpO_2_ is <90 % during at least 5 s between 30 s and 5 min after the onset of intravenous injection of the study drug in the immediate aftermath of a GTCS of 33 % in the control group [18] and 11 % in the naloxone group, 69 patients should be included in each group to reject the null hypothesis in 90 % of cases, with a 95 % CI ranging from 0.077 to 0.547. With a proportion of unusable records for technical reasons of 20 % being expected, 166 patients will be randomized. Because we anticipate that 25 % of patients eligible for inclusion will have a sGTCS during long-term video-EEG monitoring, we will need to include 700 patients.

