### Statistical analyses

The primary analysis will be based on the intention-to-treat principle, including all randomized patients with usable records for SpO_2_. The proportion of patients whose SpO_2_ is <90 % during at least 5 s between 30 s and 5 min after the onset of intravenous injection of the study drug in the immediate aftermath of a GTCS will be presented in each group (naloxone and placebo) with the corresponding exact 95 % CI. These proportions will be compared between the two groups using Pearson’s chi-square test (or Fisher’s exact test if conditions for the chi-square test are not fulfilled).

A per-protocol analysis of the primary endpoint will also be performed in the population, which will comprise all randomized patients with usable records for SpO_2_ having no major protocol deviation such as patients in whom the onset of intravenous injection of the study drug was within the 2 min following the end of the seizure (whereas those in whom the study drug was administered >120 s after the end of the seizure will be excluded). Secondary endpoints will be compared between groups using Pearson’s chi-square test, Fisher’s exact test, Student’s *t* test, or the Wilcoxon-Mann–Whitney test, depending on the variable studied. The significance level will be set at 0.05.

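### 69 patients per group gives 85.7 %, not 90 %, power for the Fisher's exact test named in the sample size section (89.6 % for the planned Pearson test), and the quoted 95 % CI is unlabelled and not reproducible

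*Protocol article*

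**What the plan says.** The Sample size section of the protocol article states the method: "Sample size was determined using Fisher’s exact test with a two-sided alternative hypothesis". It sets a two-tailed significance level of 5 % and assumes that the primary endpoint occurs in "33 % in the control group" and "11 % in the naloxone group". From these inputs it concludes that "69 patients should be included in each group to reject the null hypothesis in" 90 % of cases. It then attaches a 95 % "CI ranging from 0.077 to 0.547", without saying which quantity the interval describes.

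The Statistical analyses section names a different primary test. "These proportions will be compared between the two groups using" Pearson's chi-square, and Fisher's exact test is used only if the conditions for the chi-square test are not met. Those conditions are not spelled out.

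**The concern.** The section gives everything needed to check the figure: test, sidedness, alpha, both rates, size per group and power. Fisher's exact test is conservative at this sample size, so it needs clearly more patients than an uncorrected chi-square or normal-approximation calculation. At 33 % against 11 %, 69 per group looks like the result of an uncorrected calculation rather than of Fisher's test.

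This paragraph is the article's only justification for the size of the trial. If the stated power does not belong to the named test, a reader cannot tell which calculation was done or what power the planned analysis has. The interval adds to the difficulty, because a reader would take it as the expected result under the assumptions and could not verify it.

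**Working it through.** **Inputs**, all from the protocol article: control rate 0.33, naloxone rate 0.11, two-sided alpha 0.05, target power 0.90, 69 per group (Sample size); 1:1 allocation (Blinding and randomization); Pearson's chi-square as primary test (Statistical analyses).

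**1. Trying to reproduce 69 at 90 %.**

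The power of a test at n per group is the sum of Bin(x; n, 0.33) × Bin(y; n, 0.11) over all pairs (x, y) for which the test gives p ≤ 0.05. Full enumeration gives:

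| n per group | Fisher, two-sided | Pearson, uncorrected |
|---|---|---|
| 69 | 85.7 % | 89.6 % |
| 70 | 86.0 % | 90.1 % |
| 78 | 89.9 % | 92.9 % |
| 79 | 90.3 % | 93.2 % |

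- With Fisher, 90 % is first reached at 79 per group, which is 10 more than stated (10/69 = 14 %).
- At 69 the type II error with Fisher is 100 − 85.7 = 14.3 %, not 10 %.
- Minimum-likelihood and doubled-tail two-sided p-values give the same Fisher result.
- Unrounded rates of 1/3 and 1/9 give 86.2 % at 69, and 78 per group are then needed. Rounding does not explain the gap.

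**2. Which calculations come near 69.**

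- Unpooled normal approximation: n = (1.960 + 1.282)² × (0.33 × 0.67 + 0.11 × 0.89) / 0.22² = 10.507 × 0.3190 / 0.0484 = 69.25, which rounds up to 70.
- Exact power of the uncorrected chi-square: 89.6 % at 69, with 90 % first reached at 70.
- Pooled normal approximation: 73. Continuity-corrected: 82.
- Two-sided Fisher at 1/3 against 10 %: 89.8 % at 68 and 90.3 % at 69, so exactly 69. The 10 % is not in the article, which states 11 %.

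Two explanations remain open: an uncorrected calculation labelled as Fisher, or a true Fisher calculation on slightly different rates.

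**3. The interval.**

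Expected events at 69 per group are 69 × 0.11 = 7.59 and 69 × 0.33 = 22.77; expected non-events are 61.41 and 46.23.

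- Odds ratio: (0.11 × 0.67) / (0.89 × 0.33) = 0.251. SE of the log = √(1/7.59 + 1/61.41 + 1/22.77 + 1/46.23) = 0.462. 95 % CI 0.101 to 0.621.
- Risk ratio: 0.11 / 0.33 = 0.333. SE of the log = √(0.89/7.59 + 0.67/22.77) = 0.383. 95 % CI 0.157 to 0.706.
- Risk difference: 0.22. SE = √(0.3190/69) = 0.0680. 95 % CI 0.087 to 0.353.

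The stated interval, 0.077 to 0.547, has midpoint 0.312 and geometric mean √(0.077 × 0.547) = 0.205. It is centred on none of 0.251, 0.333 or 0.22. Score, Newcombe, Agresti-Caffo and conditional exact versions, at 66, 69 and 83 per group, do not give it either. For example, the conditional exact odds-ratio interval for 8 against 23 events of 69 is 0.094 to 0.682.

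**The case against.** **The Fisher shortfall hardly touches the planned analysis.** This stands. Pearson's chi-square is the primary test. Under the assumed rates the smallest expected cell count is (7.59 + 22.77)/2 ≈ 15, well above the customary threshold of 5 (an assumption, since the article does not state its condition). The Fisher fallback is therefore very unlikely to be used, and 89.6 % is close to 90 %. A reader might infer from the 79 per group that the trial is undersized and must recruit more. The article does not support that: 79 is what the named sizing test needs, not what the planned test needs.

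**The method may be correctly named and the inputs slightly off.** This cannot be excluded, because Fisher at 1/3 against 10 % gives exactly 69, and the Background does describe the control rate as one-third. For the same reason it would be wrong to ask the sponsor simply to declare that the size was derived from Pearson's test, since the article does not show that it was. The mismatch between the printed inputs and the printed result remains either way.

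**The interval enters no decision and may describe some other quantity.** Both are fair, so the supportable statement is that it is unlabelled and not reproducible for the standard measures and methods tried. A reader might also infer that it overstates the expected precision. It does not. On the log scale its width is ln(0.547/0.077) = 1.96, against 1.82 for the odds ratio and 1.50 for the risk ratio. As a risk difference its width would be 0.47, against 0.27. It is wider in all three cases.

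**Conclusion.** The point holds as an error of reporting in the sample size paragraph. At 33 % against 11 % and two-sided alpha 5 %, 69 per group gives 85.7 % power with Fisher's exact test, 4.3 points below the figure stated for it. With the planned Pearson test the power is 89.6 %, 0.4 points below. The named sizing test, the size and the planned analysis are therefore inconsistent, but the practical loss for the planned analysis is small. The quoted interval cannot be matched to the odds ratio, risk ratio or risk difference.

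These figures assume 69 evaluable patients in each group and the rates as printed. Whether the loss allowance delivers 69 evaluable patients per group is a separate question and adds no weight here. The cause of the mismatch cannot be settled from the article. The correction is worth making, but it is not critical: it changes no patient number, test, alpha or decision rule.

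**What to change.** 1. Re-run the calculation and report the test, rates and formula or software method actually used.
2. Without adding patients, restate the power at 69 evaluable per group for the planned analysis: 89.6 % with Pearson's chi-square at 33 % against 11 %. If Fisher's exact test is kept as the basis, state 85.7 %.
3. Replace the interval by a labelled and reproducible one, for example an expected risk difference of 22 percentage points with 95 % CI about 9 to 35 at 69 per group, or delete it.

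The cost is a short recalculation and a change of wording. The stated power becomes slightly less favourable, and design, recruitment and analysis stay as they are.

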**Methods/design:**

The Efficacy of Naloxone in Reducing Postictal Central Respiratory Dysfunction in Patients with Epilepsy (ENALEPSY) study is a multicenter, double-blind, randomized, placebo-controlled trial conducted in patients with drug-resistant focal epilepsy who are undergoing long-term video-electroencephalogram (EEG) monitoring (LTM) in an epilepsy monitoring unit (EMU). We plan to randomize 166 patients (1:1) to receive intravenous naloxone (0.4 mg) or placebo in the immediate aftermath of a GTCS. Because inclusion in the study needs to take place prior to the occurrence of the GTCS, and because such occurrence is observed in about one-fourth of patients undergoing LTM, we plan to include a maximum of 700 patients upon admission in the EMU. The primary endpoint will be the proportion of patients whose oxygen saturation is <90 % between 1 and 3 min after the end of a GTCS. Secondary outcomes will include the following: the proportion of patients who show postictal apnea, the occurrence and duration of postictal generalized EEG suppression, the total duration of the postictal coma, postictal pain, and the number of patients who have a second GTCS within 120 min after the intravenous injection.

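### The 20% allowance for unusable records is added to 138 rather than divided out, so 166 randomized patients leave about 66 evaluable per group instead of 69; the cost is about 2 points of power

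*Protocol article*

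**What the plan says.** The Sample size section of the protocol article sets out the calculation in this order.

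- Test: "Sample size was determined using Fisher’s exact test with a two-sided alternative hypothesis".
- Error rate: "For a significance level of 5 % (two-tailed").
- Event proportions: "of 33 % in the control group" and "11 % in the naloxone group".
- Base size: "69 patients should be included in each group to reject the null hypothesis in 90 % of cases".
- Loss: 20% of records are expected to be technically unusable, and the section then concludes "being expected, 166 patients will be randomized".
- Inclusions: 25% of patients are expected to have a qualifying seizure, which leads to 700 inclusions.

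The abstract repeats the target: "We plan to randomize 166 patients (1:1").

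The Statistical analyses section defines the primary analysis set as "including all randomized patients with usable records for" SpO2. It names Pearson's chi-square test for the primary comparison, with Fisher's exact test as the fallback.

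**The concern.** The 69 per group is stated before any loss is considered, so it is the number that must reach the analysis. A patient without a usable SpO2 record does not reach it, because the primary analysis set excludes such patients. The 20% is therefore a fraction of the patients randomized, and the number to randomize is the evaluable number divided by 0.80. The plan's 166 is what results when 20% of the evaluable number is added on top, and that always gives too few.

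At stake is whether the headline recruitment target delivers the plan's own required analysis set, and whether the stated power describes the analysis that will be run. The type I error, the endpoint and the choice of test are not affected.

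**Working it through.** **Inputs**, all from the protocol article: 69 per group, 138 in total (Sample size); loss 20% (Sample size); 166 randomized 1:1, 83 per group (Sample size, Abstract); 33% versus 11%, two-sided 5% (Sample size); primary set limited to usable records (Statistical analyses).

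**1. Reproducing the plan's figure**

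- Multiplying: 138 × 1.20 = 165.6, rounded up to 166. Per group: 69 × 1.20 = 82.8, rounded up to 83. This matches exactly.
- Dividing: 138/0.80 = 172.5, rounded up to 173. Per group: 69/0.80 = 86.25, rounded up to 87, or 174 in total. This does not match.

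The article gives no other basis for 166.

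**2. What 166 delivers**

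- In total: 166 × 0.80 = 132.8, against 138 required, about 5 short.
- Per group: 83 × 0.80 = 66.4, against 69.
- Break-even loss: 1 − 138/166 = 16.9%. The plan reaches 69 per group only if the loss stays at or below that, which is under its own 20%.
- Shortfall in randomized patients: 173 − 166 = 7, or 174 − 166 = 8 if each group is rounded up.

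**3. Effect on power**

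Exact power is the sum, over all pairs of event counts (i, j), of Bin(i; n, 0.33) × Bin(j; n, 0.11) for those pairs that the test rejects at two-sided 5%. Pearson's test is taken without continuity correction. The normal approximation uses the pooled variance under the null hypothesis.

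| Method | 69 per group | 66 per group | Loss |
|---|---|---|---|
| Pearson, exact enumeration | 89.6% | 88.0% | 1.6 points |
| Fisher, exact enumeration | 85.7% | 83.6% | 2.1 points |
| Normal approximation, pooled | 88.5% | 87.1% | 1.4 points |

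**4. Separating the two sources of the gap to 90%**

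- Fisher: 90 − 83.6 = 6.4 points. Of these, 90 − 85.7 = 4.3 exist already at 69 per group, and 2.1 come from the inflation step.
- Pearson: 90 − 88.0 = 2.0 points. Of these, 0.4 exist at 69 per group, and 1.6 come from the inflation step.

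**5. Inclusions**

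- At the planned 25%: 174/0.25 = 696, and 700 × 0.25 = 175. The corrected target would just fit.
- The Study conduct section says that unsupervised seizures do not lead to randomization, and Trial status reports 16 randomized of 157 included, i.e. 16/157 = 10.2%. At that rate 8 more randomizations need 8 × 157/16 = 78.5, about 79 more inclusions. Some of the 157 may still have been under monitoring, so 10.2% may be too low.

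**The case against.** The strongest case on the other side is that the slip hardly matters. It costs about 5 evaluable patients and 1.4 to 2.1 points of power. The 20% is a planning allowance, and the article describes SpO2 measurement as reliable in most seizures, so the actual loss could be below 16.9%, in which case 166 would suffice. This stands as an argument about severity. It does not rescue the sentence, which states a base size, a loss rate and a total that do not agree with one another.

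One could also read the 20% as a margin on the required number. The plan, however, describes it as a proportion of records, which is naturally taken over the records obtained, and the analysis set removes the unusable ones.

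A reader might infer three stronger things that the article does not support:

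- *That the inflation step explains the whole distance from 90% to 83.6% under Fisher's test.* About two thirds of it (4.3 of 6.4 points) is present at the full 69 per group, because 69 does not give 90% power with the test named for the sample size; about 79 per group would be needed.
- *That randomizing 174 makes the 90% statement true.* It restores 69 per group, hence 85.7% under Fisher's test and 89.6% under Pearson's.
- *That 174 costs nothing because 700 inclusions cover it.* That holds only if every expected seizure leads to randomization, which the supervision rule and the early count both put in doubt.

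**Conclusion.** The point holds and is minor (should-fix). The allowance was applied as 138 × 1.20 instead of 138/0.80, and at the plan's own 20% loss the 166 patients yield about 132 evaluable (66 per group) rather than 138 (69 per group).

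The effect of this error alone is 1.6 points of power under Pearson's test, which is the primary test, and 2.1 points under Fisher's. Pearson's figure is the more relevant one for the planned analysis: at 66 per group and an average event proportion of 22%, the expected event count per group is 66 × 0.22 = 14.5, so the fallback to Fisher's test should not be needed under the usual expected-count rule (an assumption, since the article does not state its condition).

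The conclusion takes the 69 per group, the 33% and 11%, and the 20% as given, with the loss equal in both groups. Whether 69 is the right base size is a separate question.

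**What to change.** Keep 166 and replace the end of the loss sentence in the Sample size section with wording such as:

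> Of the 166 randomized patients, about 132 (66 per group) are expected to be evaluable if 20% of records are unusable, giving about 88% power with Pearson's chi-square test (84% with Fisher's exact test).

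This costs one sentence and a slightly less favourable stated power. The target in the abstract, the randomization and the analysis stay as they are.

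The alternative is to raise the target to 173, or 174 with 87 per group, in both the Sample size section and the abstract. That is 7 to 8 more randomizations and restores 69 evaluable per group. If this route is taken, the power statement still needs rewording, because 69 per group gives 85.7% and not 90% under Fisher's test. The 700 inclusions, which the abstract calls a maximum, should also be rechecked against the proportion of included patients actually being randomized.

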### Study conduct

All included patients will benefit from continuous monitoring of SpO_2_ and will be have a peripheral venous catheter inserted throughout the video-EEG/video-SEEG. During video-EEG/video-SEEG, patients are continuously supervised by one or two specialized nurses during the daytime at all participating centers. This continuous supervision allows immediate intervention in case of occurrence of a seizure. In six centers, patients are supervised by one specialized nurse during the night, whereas they are not supervised in the other centers. Given this organization of some EMUs, a GTCS might occur during a period without supervision. Unsupervised GTCS will not result in randomization, and the patient will remain eligible for randomization in case of occurrence of another GTCS during the monitoring. Inclusion in the study will not modify antiepileptic drug withdrawal, the management of which will remain at the discretion of each center.

In case of occurrence of a GTCS, patients will be randomized (1:1) into one of two groups: a single dose of 1 ml of either (1) naloxone or (2) placebo will be administered by the supervising nurse or physician, using direct intravenous injection. The evolution from a focal seizure to a GTCS being gradual, and the total duration of the seizure ranging from 2 to 3 min, the injection will be prepared during the course of the seizure. Given the assumptions about the role of endogenous opioid release in the spontaneous termination of seizures, naloxone will be administrated immediately after the end of the GTCS and not before. Specifically, treatment administration will be performed within the 2 min following the end of the GTCS.

Immediately after the administration of the treatment, the supervising nurse or physician will monitor respiratory movements to detect absence of chest expansion, SpO_2_, heartbeat and blood pressure, recovery of consciousness and pain, using a visual analogue scale. In patients with SpO_2_ < 85 % during >2 min after the injection of the study drug, O_2_ will be administered using a high-concentration breathing mask (15 L/min). Occurrence of one or more GTCSs during the 2 h following treatment administration will be monitored.

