### Trial status

The study protocol was designed in September 2013 and funded by the French Ministry of Health in 2014. The study was registered with ClinicalTrials.gov (NCT02332447) in January 2015. The first participant was enrolled on 26 June 2015. A total of 157 patients have been included so far, of whom 16 have been randomized.

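### The 25 % behind the 700-patient maximum is a seizure rate, not a randomization rate; at the yield the article itself reports, 700 inclusions project to about 71 randomized (42–112), not 166

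*Protocol article*

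**What the plan says.** The Sample size section of the protocol article asks for 69 evaluable patients per group and adds an allowance for 20 % unusable records to reach 166 randomized. It then expects that 25 % of eligible patients "will have a sGTCS during long-term video-EEG monitoring, we will need to include 700 patients". The abstract makes that number a ceiling: "we plan to include a maximum of 700 patients upon admission in the EMU".

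The conditions for randomization are set elsewhere. Under Participants, a patient is randomized only if the sGTCS occurs under the supervision of a nurse or physician, and an opioid dose given after inclusion suspends eligibility for 12 h. Study conduct repeats the first condition: "Unsupervised GTCS will not result in randomization". The patient does stay eligible for a later GTCS. On cover at night, the same section says: "In six centers, patients are supervised by one specialized nurse during the night, whereas they are not supervised in the other centers". Study setting gives 15 centers, so nine have none.

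Trial status reports progress: "A total of 157 patients have been included so far, of whom 16 have been randomized".

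**The concern.** The conversion from inclusions to randomizations has a single factor, the proportion of monitored patients with at least one sGTCS. That proportion is an upper limit on the share who can be randomized, because supervision and the opioid window can only reduce it. The Sample size section has no term for either, and the accrual reported in the same article is well below what the plan needs.

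If 700 is a true maximum, inclusion would end well short of 166 randomized patients at the reported yield. The 90 % power would then not describe the trial being run, and a non-significant result would say little about an effect of the assumed size.

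**Working it through.** **Inputs (protocol article).** Sample size: 33 % versus 11 %, two-sided 5 %, 69 per group, 90 % power, 20 % unusable records, 166 randomized, 25 % with an sGTCS, 700 included. Study setting and Study conduct: 15 centers, six with night supervision. Trial status: 157 included, 16 randomized.

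**1. The plan's own figures.**
- Per group: the unpooled normal formula gives (0.33 × 0.67 + 0.11 × 0.89) × ((1.960 + 1.282)/0.22)² = 69.3, which agrees with 69. By exact enumeration, power at 69 per group is 0.896 for the Pearson chi-square test (the planned primary test) and 0.857 for Fisher's exact test (the test named for sizing).
- Randomized: 138 × 1.2 = 165.6, so 166.
- Included: 166/0.25 = 664, stated as 700. In the other direction, 700 × 0.25 = 175.

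The inclusion step is correct as arithmetic. Its slack is 175 against 166, so 166/175 = 95 % of patients with an sGTCS would have to be randomized.

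**2. Reported yield against required yield.**
- Required: 166/700 = 23.7 %.
- Reported: 16/157 = 10.2 %, Clopper–Pearson 95 % CI 5.9–16.0 %.
- Probability of 16 or fewer out of 157: 1.2 × 10⁻⁵ if the true yield is 23.7 %, and 2.5 × 10⁻⁶ if it is 25 %.
- To reach 166, the remaining inclusions would have to yield (166 − 16)/(700 − 157) = 150/543 = 27.6 %, more than the 25 % assumed to have any sGTCS. Even at 25 % from here on, the total is 16 + 543 × 0.25 = 152.

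**3. What 700 inclusions project to at the reported yield.** Randomized = 700 × yield; evaluable per group = randomized × 0.8/2; power by exact enumeration for 33 % versus 11 %.

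| Yield | Randomized | Evaluable per group | Chi-square | Fisher |
|---|---|---|---|---|
| 5.9 % (lower limit) | 42 | 17 | 0.33 | 0.21 |
| 10.2 % (reported) | 71 | 28 | 0.52 | 0.39 |
| 16.0 % (upper limit) | 112 | 45 | 0.75 | 0.64 |

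Reaching 166 at 10.2 % would take 166/0.1019 = about 1,630 inclusions (about 1,040 to 2,800 over the interval).

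**4. What the supervision rule alone would give.** The documents give no night share of seizures and no center sizes. Assume equal centers, one sGTCS per patient, and a night share s of 1/3, 1/2 or 2/3. The supervised share is (6 + 9 × (1 − s))/15 = 0.80, 0.70 or 0.60, so 175 × share = 140, 122 or 105 randomized. If instead every such patient had two independent events (an optimistic assumption), the share is (6 + 9 × (1 − s²))/15, giving about 163, 149 or 128. All of these are below 166 and all are above 71.

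**5. Patients still being monitored.** Study duration puts monitoring at 21 days at most. If 5 to 15 of the 157 had not finished (assumption), the projection is 74 to 79 randomized. If 30 had not (assumption), 16/127 projects to 88, and the probability of so few at a 25 % yield is still 0.0004.

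**The case against.** The strongest reply is that power is tied to the 166 randomized. On this view 700 is only a recruitment forecast, made when the trial was designed in September 2013, before any yield had been seen. Raising it would restore the target, and a shortfall costs precision without biasing the comparison. This stands in part: the comparison remains valid, and the proportions will still be reported with exact intervals. But the abstract calls 700 a maximum, and the Sample size section still offers it as sufficient beside a status line that contradicts it.

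A second reply is that continued eligibility after an unsupervised GTCS recovers some of the loss. That is right, and step 4 shows that it could recover much of it. Nothing in the document shows that it restores the 95 % needed.

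A reader might infer that the supervision rule by itself brings the trial down to 71. The documents do not support that. It would need only about 41 % of patients with an sGTCS to be randomizable (71/175), a figure that appears nowhere, and the rule alone gives 105 or more on the assumptions above. A lower sGTCS rate, the opioid window, missed injections and unfinished monitoring may also contribute, and the document does not separate them.

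A reader might also take 71 as the certain outcome, or a null result as worthless. The 71 is a projection from 16 events, undated in the article, and assumes that the early yield persists. A null result would be weakly informative, not without meaning.

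**Conclusion.** The point holds as a wrong input to the sample size: the share with any sGTCS is used where the share who can be randomized is needed, in conflict with the protocol's own conditions for randomization. The reported 10.2 % is incompatible with the required 23.7 %, and even the upper confidence limit gives only 112 randomized. At the reported yield, the 700 maximum corresponds to power of about 52 % by chi-square (33–75 % over the interval) or about 39 % by Fisher (21–64 %), not 90 %.

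These figures assume a constant yield, 20 % unusable records, equal groups and the plan's own event rates. The cause of the shortfall is not established.

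**What to change.** In the Sample size section:

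- Replace 25 % with the proportion of included patients who have a supervised, randomizable sGTCS, using the observed yield pooled over both groups (16/157 at the time of the article, or a later count) with its 95 % CI.
- State the number randomized and the power that a maximum of 700 delivers, as a range and naming the test. On present figures: about 71 randomized (42–112), with power of about 52 % (33–75 %) by chi-square or about 39 % (21–64 %) by Fisher.
- Remove the statement that 700 inclusions are enough for 166 randomized, and align the abstract with the revised text.

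The yield is counted before treatment and pooled over groups, so reassessing it needs no unblinding and costs no alpha. The cost is revised wording and a less favourable stated power. Whether to raise the maximum or extend recruitment beyond July 2018 is a separate decision for the sponsor.
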